### Recruitment

Patients who are about to complete or have recently completed cancer therapy (see inclusion criteria), will be informed about the possibility to participate in the trial by their oncologist or the nursing staff. If a patient is interested in participating in the trial, the patient's name and telephone number will be forwarded to the study nurse after written consent has been given. The study nurse will contact the patient, inform him or her orally and in writing about the trial (goals/randomisation/intervention) and clarify the inclusion and exclusion criteria (Figure 1). In order to determine the patient's distress level, the distress thermometer is used [24]. A score above 3 on a Likert scale ranging from 0-10 indicates 'distress'; a score above 7 indicates severe 'distress' and requires medical psychiatric treatment. Severely distressed patients will not be included in the trial, which means that patients with depression can likely be ruled out.

**Figure 1 F1:**
[figure not shown]
**Workflow of trial**.

### Randomisation

Treatment allocation will be done by random permutation within blocks with block sizes of 2 and 4. In addition to the block randomization allocation will be stratified according to the type of carcinoma (breast carcinoma, colon carcinoma, Hodgkin and Non Hodgkin lymphoma and one group with "other tumor types") thus allowing for an even distribution of the intervention through the most common expected tumor types with regard to the participating centres various diagnoses. As the size of the participating centres is not necessarily related to the contribution of the participating centres regarding the patient recruitment we will not perform a randomisation stratified by centre. The randomisation is done independently of centres, rehabilitation coaches and the study nurse. The study nurse is responsible for providing patients with detailed information; additionally, they are in charge of the assessment.

The randomisation is performed with STATA statistic program. The relevant information is only accessible to an employee of the Institute of General Practice and Health Services Research who is not involved in the trial. After the inclusion of a patient in the trial and the baseline assessment, the study nurse receives information concerning the allocation of patients to the intervention or control arm by sequentially numbered opaque sealed envelopes. Therefore, the blinding regarding the allocation is guaranteed.

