### Design

The trial is a multicentre, two-arm randomised controlled study. Patients are randomised parallel in either 'usual care' plus case management or 'usual care' alone.

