### Inclusion criteria for patients

a) Age ≥18 years

b) Completion of a therapy with chemo- and/or radiotherapy/surgery (longer term hormone and antibody therapy are excluded)

c) Therapy with curative intention

d) Patients with an expected survival time >1 year

e) Increased distress score (3-7 on the Distress Thermometer Likert scale)

f) Intention to undertake ambulant rehabilitation

g) Rehabilitation need/prevailing strain

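### Blocks of 2 and 4 within tumour strata, with the screening nurse receiving each allocation, do not support the statement that allocation blinding is guaranteed

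*Protocol article*

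**What the plan says.** Protocol article, Randomisation: "Treatment allocation will be done by random permutation within blocks with block sizes of 2 and 4". The strata are breast carcinoma, colon carcinoma, lymphoma (Hodgkin and non-Hodgkin) and other tumours. Centre is not a stratum: "we will not perform a randomisation stratified by centre". The list is produced in STATA and can be seen only by an institute employee who has no part in the trial.

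The study nurse appears at three points:

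- Under Recruitment, the nurse contacts each referred patient, explains the trial and is to "clarify the inclusion and exclusion criteria".
- Under Randomisation, the nurse is also responsible for assessments.
- Once a patient is included and baseline is done, the nurse learns the assigned arm from numbered, opaque, sealed envelopes.

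The Randomisation section then concludes: "Therefore, the blinding regarding the allocation is guaranteed".

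One entry criterion leaves visible room for judgement: "Rehabilitation need/prevailing strain" (Inclusion criteria for patients).

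**The concern.** Concealment has two parts: nobody should see the list in advance, and nobody who decides on entry should be able to infer the next assignment from past ones. The safeguards described deal with the first part only. With no stratification by centre, each tumour stratum appears to run as one sequence across all eleven centres. The person who screens the next patient has been told the earlier results. Very small blocks force the arms back into balance quickly, so the running tally carries information about the next assignment.

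Case management against usual care cannot be masked from patients, and the primary outcome is a patient questionnaire, so concealment at entry is a main protection for the comparison. If entry or its timing were influenced by the arm expected next, the groups could differ at baseline in motivation or prognosis. The planned regression would adjust only for differences that were measured.

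**Working it through.** The article gives no figure for predictability, so there is nothing of its own to reproduce.

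**Inputs.** Block sizes 2 and 4 (Randomisation). Two arms (Design); a 1:1 ratio is assumed because it is not stated. The mix of sizes is not stated either, so equal numbers of 2- and 4-blocks are assumed and the share of 2-blocks is then varied from 25% to 75%. Enrolment is 132 (Sample size).

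**Guessing rule.** Name the arm that is behind in the stratum, and toss a coin when the arms are level. This needs only the tally, not the block sizes.

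**Formulas for a block of 2m patients.**

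- Expected allocations made while the arms are level: B = 4^m / C(2m, m) − 1.
- Every block returns to balance, so exactly m steps go towards balance. All of them are guessed correctly, and all occur while the arms are unequal.
- Expected correct guesses: m + B/2.
- Expected allocations that are certain if the block boundary is known: 2m/(m + 1).

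| Block | B | Correct guesses | Certain, boundary known |
|---|---|---|---|
| 2 | 1 | 1.5 of 2 (75.0%) | 1 |
| 4 | 5/3 | 17/6 of 4 (70.8%) | 4/3 |
| 6 | 2.2 | 4.1 of 6 | 1.5 |
| 8 | 2.657 | 5.329 of 8 | 1.6 |

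**Blocks 2 and 4, equal numbers (6 patients per pair).**

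- Correct overall: (1.5 + 17/6)/6 = 13/18 = 72.2%.
- Unbalanced before allocation: (6 − 8/3)/6 = 55.6%.
- Correct when unbalanced: 3/(10/3) = 90%.
- Certain with known boundaries: (1 + 4/3)/6 = 7/18 = 38.9%.
- Certain when only the two sizes are known, not their order: about 10% (by simulation).

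**Other mixes of 2 and 4.** With 25% and 75% of blocks of size 2:

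- Overall: 2.5/3.5 = 71.4% and 1.8333/2.5 = 73.3%.
- When unbalanced: 1.75/2 = 87.5% and 1.25/1.3333 = 93.8%.
- Simulation for stratum sizes from 10 to 132, with a guesser who knows the two sizes but not their order: 70% to 73% correct overall, 6% to 14% certain.

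**Blocks 4, 6 and 8, equal numbers (18 patients per set), for comparison.** The sum of B is 1.667 + 2.2 + 2.657 = 6.524.

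- Correct overall: (9 + 3.262)/18 = 68.1%.
- Unbalanced before allocation: (18 − 6.524)/18 = 63.8%.
- Correct when unbalanced: 9/11.476 = 78.4%.
- Certain with known boundaries: (1.333 + 1.5 + 1.6)/18 = 24.6%.

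**In patients.** Ignoring incomplete last blocks, expected correct guesses among 132 are 132 × 0.722 = 95 for blocks of 2 and 4, 132 × 0.681 = 90 for blocks of 4, 6 and 8, and 66 by chance.

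**The case against.** A reader might infer that the next assignment is largely known and that selective entry follows. The documents do not support that, for these reasons:

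- About 44% of allocations remain coin tosses even for someone who tracks the tally. The second place in a block of 2 is certain only to someone who knows that the block has size 2, and mixing sizes hides this. The article does not say that the nurse knows the sizes.
- The text says that the nurse receives the allocation by envelope. It does not say who stores or opens the envelopes, nor that a single person follows every stratum.
- Discretion is limited. Oncologists or nursing staff refer patients first, distress is a numeric score with set limits, intention to undertake rehabilitation is the patient's own, and therapy must have ended no more than a month before.
- Baseline is assessed before the arm is disclosed, regression on baseline differences is planned, and patients mail their questionnaires to the study centre themselves.
- Small blocks within tumour strata are a defensible trade of predictability for balance.

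All of this stands, and it reduces the size of the concern. It does not remove it. Each limit leaves some room in whether and when a patient is entered, baseline assessment before disclosure does not prevent foresight, and regression cannot reach unmeasured selection. None of it supports the word guaranteed.

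A reader might also take the fall from 90% to 78% as the benefit of larger blocks. That overstates it: strata are then unbalanced more often (64% against 56% of allocations), and the overall rate falls only from 72% to 68%.

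**Conclusion.** The article claims a property that the described procedure does not have. On its stated block sizes, a simple tally lifts correct guessing from 50% to about 72% overall, and to 90% in the 56% of allocations made while a stratum is unbalanced. The figures rest on 1:1 allocation, equal numbers of the two block sizes, and a nurse who sees and remembers the earlier results in each stratum. The overall rate moves little, 70% to 73%, over the mixes and stratum sizes tried. Certainty about the next arm is much rarer: about 39% of allocations with known boundaries, and about 10% if only the sizes are known.

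The finding is an opportunity for selection bias. Nothing in the article shows that selection took place. The point is worth acting on because the trial cannot be masked, its primary outcome is self-reported, and the change is cheap.

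**What to change.** 1. For patients not yet allocated, regenerate the STATA list without blocks of 2. Use larger blocks in random order (for example 4, 6 and 8) and do not disclose the sizes to the study team. The gain is modest, as shown above. The cost is a new list and slightly more possible imbalance within each stratum.
2. Where existing staff allow, have eligibility confirmed and recorded by someone unaware of earlier allocations. For example, the uninvolved employee could send each allocation to the coaching side rather than to the screening nurse. This acts on the tally itself. Releasing allocations by phone or e-mail to the same nurse would not, since the nurse would still learn every result. The cost is some reorganisation, including who tells control patients their arm.
3. Replace the sentence claiming a guarantee with a statement that the list is concealed until inclusion and baseline are complete, and that the trial is open from then on. This costs nothing.

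### The study nurse who checks eligibility and runs the assessment learns every allocation; someone else already in place could release it instead

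*Protocol article*

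**What the plan says.** Three duties fall to one role in the protocol article.

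- **Screening.** Under Recruitment, the study nurse contacts interested patients, explains the trial and will "clarify the inclusion and exclusion criteria".
- **Assessment.** Under Randomisation, the study nurses inform patients in detail; "additionally, they are in charge of the assessment". No visit is named.
- **Receipt of the allocation.** Randomisation also states that "the study nurse receives information concerning the allocation of patients to the intervention or control arm by sequentially numbered opaque sealed envelopes". This step comes once the patient is enrolled and baseline is complete. The section then concludes that "the blinding regarding the allocation is guaranteed".

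The same section seeks separation elsewhere: "The randomisation is done independently of centres, rehabilitation coaches and the study nurse". It also leaves the list with one institute employee who has no part in the study. Assignment is by permuted blocks of 2 and 4 within tumour-type strata.

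**The concern.** Opaque envelopes opened after inclusion protect the patient now being enrolled. They do not stop the person who opens them from building up a record of past assignments. Here that person also judges whether the next patient is eligible. With small blocks, that record says a good deal about the next assignment.

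Knowledge of the likely arm matters only if there is room to act on it, and there is some. The inclusion criteria ask for a rehabilitation need and for an intent to take up outpatient rehabilitation. One exclusion criterion turns on whether great distress is apparent. The nurse also explains the trial to the patient before enrolment. A screener who expects a given arm could, even without meaning to, be stricter or more persuasive. At stake is the comparability of the arms at entry.

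A second, smaller matter is that the role named for assessment is unblinded after baseline for whatever it then handles.

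**Working it through.** The plan gives no figure on this point, so the check is of how much the nurse's knowledge reveals.

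**Inputs.** Block sizes 2 and 4 within strata by tumour type (Randomisation). Assumptions: 1:1 allocation, both block sizes equally likely, and one nurse who tracks the earlier allocations in each stratum. The article does not give the mix of block sizes.

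**Guessing rule.** Name the arm that is behind in the stratum; toss a coin when the arms are level. The arms are level at the end of every block, so the rule needs no knowledge of block boundaries or sizes.

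**Block of 2.** The first guess is right with probability 1/2, the second with probability 1. Expected correct: 1/2 + 1 = 1.5 of 2, or 75%.

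**Block of 4.**
- First: 1/2.
- Second: two of the three remaining places belong to the other arm, so 2/3.
- Third: the arms are level with probability 2/3 (guess right 1/2 of the time) and two apart with probability 1/3 (guess always right), so 2/3 × 1/2 + 1/3 × 1 = 2/3.
- Fourth: 1.

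Expected correct: 1/2 + 2/3 + 2/3 + 1 = 17/6, or about 2.83 of 4 (70.8%).

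**Both sizes equally likely.** (1.5 + 17/6) / (2 + 4) = 4.33 / 6 = 72.2%, against 50% by chance.

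**Range over the unknown mix.** From 70.8% (all blocks of 4) to 75% (all blocks of 2), so the result hardly depends on this assumption.

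**Simulation.** 4,000 sequences under the same rule gave 71.6% for 33 allocations (132 planned patients over four strata, taken as equal in size) and 72.2% for 132 allocations in one sequence.

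**Follow-up.** Outcome measures sets data collection at months 0, 3, 6 and 12. Disclosure comes after month 0, so any later assessment handled by the nurse is handled with the arm known. Data security states that patients mail the questionnaires directly to the study centre. The answers to FACT-G therefore do not pass through a nurse's rating, and patients know whether they have a coach.

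**The case against.** Several stronger readings are tempting, and the document does not support them.

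- **That the stated blinding is false.** The sentence speaks of blinding with regard to the allocation and follows directly from envelopes opened after inclusion and baseline. In context it means allocation concealment, which the procedure can provide for the patient concerned. Nowhere does the article claim blinded assessors, patients or coaches. The term is loose, not a false claim.
- **That all assessments at months 3, 6 and 12 are run by an unblinded nurse.** The article does not say which assessments the nurse handles, and the workflow figure is not shown.
- **That arm-dependent chasing of questionnaires produces differential missing data.** No section gives the nurse the tasks of chasing non-responders or of classifying contacts as planned or unplanned. This is possible, not shown.
- **That the next allocation is certain.** In a block of 2 the second assignment is certain only to someone who knows the block size. With sizes unknown, certainty arises only after two like assignments that start from balance. That opens 1/3 of blocks of 4 and fixes the next two places: (1/3 × 2) / 6 = 1/9 of allocations if sizes are equally likely.
- **That the change is free.** It is not; its costs are set out with the fix.

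It is also fair to say that oncologists and nursing staff make the first approach, that the nurse does not coach, and that hiding the arm from the nurse leaves the openness of a self-reported primary outcome as it is.

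All of this stands, and it narrows the point. It does not remove the fact that the person who decides on eligibility holds the allocation history.

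**Conclusion.** The concern holds in a limited form. The role that checks eligibility and is responsible for assessment is told every allocation. The firmer consequence is for selection of later patients: about 72% of next allocations can be guessed (70.8% to 75% across possible block mixes), against 50% by chance, where several entry criteria call for judgement. This assumes that the nurse tracks assignments within strata; with several nurses who do not share that information, the figure would be lower. It measures predictability, not bias. The size of any resulting bias cannot be derived from the document, and nothing in it suggests that screening is in fact influenced.

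The consequence for outcome data is weaker. The nurse is unblinded for any assessment handled after baseline, but its extent is not stated and the effect on the FACT-G answers is limited. The point calls for a cheap improvement and a clearer sentence. It is not a flaw that invalidates the design.

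**What to change.** Change the last step under Randomisation. Once the nurse has reported inclusion and a completed baseline, someone already in place other than the study nurse releases the allocation to the coach and the patient. The institute employee who holds the list is an obvious choice. The nurse is not told.

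Replace the blinding sentence with:

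> Allocation is concealed until inclusion; the study nurse is not informed of the arm; patients and coaches are not blinded.

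**Cost.** No new staff, and no change to sample size, significance level or analysis. The employee, described as outside the trial, takes on a small trial task and needs access to patient contact data, which Data security now limits to direct members of the internal study team. Patients wait a little longer for their result. Inclusion has begun, so this would be a change of workflow within a running trial, and the date of the change should be recorded. Patients may still reveal their arm to the nurse, so the change reduces the nurse's knowledge without ensuring ignorance.

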### Statistical analyses

Continuous primary and secondary outcomes will be checked by the Shapiro-Wilk test for normality distribution and data are expressed by means with standard deviations and medians with interquartile range as appropriate. Categorical variables will be expressed as percentages. Primary and secondary outcomes will be compared between groups to investigate the effect of the case management on oncology rehabilitation using parametric or non-parametric tests as appropriate. Categorical outcomes will be analysed by Chi Square tests. To control for any imbalance between groups multiple regression analysis will be used and measures that show any difference in baseline characteristics will be included into the model as potential confounders.

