### Sample size

The power calculation was based on the following data: mean value in primary outcome (FACT) 22.7, a variation of 3.0 units in the FACT-score is considered clinically relevant and is thus imputed as minimal difference (effect) to be achieved. The standard deviation of FACT is 5.4 according to literature; the level of significance was set at 0.05, also a power at 0.8. The power analysis revealed a sample size of 102 patients. Assuming a drop-out rate of 30% due to the severely ill patient population, 132 patients would need to be enrolled. The calculation of the sample size was done with the aid of Southwest Oncology Group computers.

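### A normality check on the outcome data in effect decides whether the primary FACT-G comparison is of means or ranks, although the trial is sized on a mean difference

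*Protocol article*

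**What the plan says.** All references are to the protocol article.

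- **Statistical analyses, normality check.** "Continuous primary and secondary outcomes will be checked by the Shapiro-Wilk test for normality distribution". The same sentence continues that "data are expressed by means with standard deviations and medians with interquartile range as appropriate".
- **Statistical analyses, group comparison.** Primary and secondary outcomes are compared between arms "using parametric or non-parametric tests as appropriate". No single test or effect measure is named for FACT-G.
- **Statistical analyses, regression.** "To control for any imbalance between groups multiple regression analysis will be used". Covariates enter if they differ between arms at baseline. The regression is not called the primary analysis.
- **Sample size.** "a variation of 3.0 units in the FACT-score is considered clinically relevant and is thus imputed as minimal difference (effect) to be achieved". The other inputs are "mean value in primary outcome (FACT) 22.7" and "The standard deviation of FACT is 5.4 according to literature", with significance level 0.05, power 0.8 and a result of 102 patients.
- **Outcome measures and Table 2.** FACT-G is the primary outcome, collected at months 0, 3, 6 and 12, so a baseline value exists for adjustment.

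**The concern.** A normality test placed ahead of an open choice between parametric and non-parametric methods has no other evident purpose than to guide that choice. The primary hypothesis (a difference in means or a shift in ranks), the summary measure (mean or median) and the p-value would then be settled only once the outcomes are in.

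This does not fit the design. The trial is built around a stated relevance threshold of 3.0 FACT units. A comparison of means yields an estimate and interval that can be read against that threshold. A rank test yields a p-value for a different hypothesis and no estimate on that scale. The trial could end with a significant or non-significant result that does not answer the question it was sized for.

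The pre-test also gains little. With about 51 patients per arm, a comparison of means does not need normal scores to hold its error rate.

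**Working it through.** **1. Reproduce the plan's own figure.** Inputs from Sample size: difference 3.0, SD 5.4, alpha 0.05, power 0.8. Sidedness is not stated. The permuted blocks of 2 and 4 across two arms imply 1:1 allocation.

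n per arm = 2 × (z_alpha + z_power)² × (SD / difference)²

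- Two-sided: 2 × (1.960 + 0.842)² × (5.4 / 3.0)² = 2 × 7.85 × 3.24 = 50.9, rounded up to 51 per arm, **102 in total**. This matches exactly.
- One-sided: the same formula gives 82 in total, which does not match.
- The exact t-test version needs 51.8 per arm (104 in total). Power at 51 per arm is 0.801 by the normal approximation and 0.793 by the t-test.

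So 102 is the size for a two-sided comparison of two means.

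**2. How often would the pre-test switch the analysis?** The article does not say whether normality is tested per arm or pooled, or at what level. Assume each arm is tested at 5% and either rejection leads to the rank test. With truly normal data the chance of a switch is 1 - 0.95² = 0.0975.

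**3. Simulation.** 6,000 trials per scenario, 51 per arm, SD 5.4, control mean 22.7. Shapiro-Wilk is run in each arm, followed by a t-test if neither arm rejects and otherwise by Mann-Whitney. The skewness values are assumptions, because the article gives no distribution.

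| Assumed shape | True difference | Switch to rank test | t-test significant | Rank test significant | Two-stage significant | t-test and rank test disagree |
|---|---|---|---|---|---|---|
| Normal | 0 | 9.4% | 5.0% | 5.1% | 5.1% | 2.1% |
| Normal | 3.0 | 9.7% | 79.0% | 76.5% | 78.8% | 6.0% |
| Skewness -0.5 | 0 | 40.7% | 5.1% | 4.8% | 5.3% | 2.2% |
| Skewness -0.5 | 3.0 | 40.9% | 79.4% | 79.7% | 80.3% | 5.6% |
| Skewness -1 | 0 | 91.0% | 5.1% | 4.8% | 5.0% | 2.8% |
| Skewness -1 | 3.0 | 90.2% | 79.7% | 84.1% | 84.2% | 7.5% |

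The Monte Carlo standard error of a 5% rate is √(0.05 × 0.95 / 6000) = 0.3 percentage points, so none of the null rates is distinguishable from 5%.

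**4. Reading the table.** The last column counts all trials in which the two tests would give different verdicts, whether or not the pre-test switched. It shows how far the verdict can depend on the choice of test. It is not the rate at which the pre-test itself changes the verdict.

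**The case against.** **The article never says that Shapiro-Wilk selects the test.** The check stands in the sentence on how data are summarised. The choice of test comes later and ends in an unspecific phrase. No level, no if-then rule and no rank test is named, and an article may leave such detail to a fuller document. This stands in part: the link is an inference and should be stated as one. But the article does more than stay silent. It sets out an approach in which the primary test and summary measure remain open, next to a normality check on the outcome itself.

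**The regression already gives an estimate in FACT units.** This stands in part. It would produce an adjusted difference comparable with 3.0, but it is tied to baseline imbalance and is not designated primary.

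**No error-rate harm is shown.** This stands fully. A reader might infer that the two-stage procedure inflates type I error, and the table does not support that. Under the more skewed shape the rank test has more power, and part of the disagreement there is true effects that the t-test misses.

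**A much larger disagreement might be inferred.** Beta-distributed scores on a 0 to 28 range, with the mean raised by 1.5 to 2.0 units and SD held at 5.4, make the two tests disagree in about 29 to 40% of trials, with the pre-test rejecting every time. The documents do not support this as a typical figure. They give no score range, and the result arises only when about 39 to 49% of the intervention arm scores the maximum. Other ways of generating the same shifts give roughly 14 to 26%. At the design difference of 3.0, with the beta precision held instead of the SD, the figure is 9.8%.

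**Conclusion.** The point holds as a moderate one. The plan lets the outcome data settle whether its primary result is a mean difference or a rank comparison, while its sample size reproduces only as a two-sided comparison of means.

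If normality is tested per arm at 5%, a switch would occur in about 9 to 10% of trials even with normal data, about 41% at skewness -0.5 and about 90% at -1. At a 3.0-unit effect the two tests disagree on significance in about 5 to 7.5% of trials under these shapes. Stronger ceiling effects would raise that figure, but by how much depends on a score distribution that the documents do not give.

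The conclusion rests on reading the normality check as guiding the choice of test, on the assumed per-arm 5% rule and, for the larger switching rates, on the assumed skewness. The mismatch between a rank test and the 3.0-unit target depends on none of the simulated shapes.

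**What to change.** Drop the normality check as a basis for choosing the FACT-G analysis. Name one primary analysis: the difference in mean FACT-G at 12 months between arms, from a linear model adjusted for month-0 FACT-G, with heteroscedasticity-robust standard errors, whatever the distribution of the scores. Report the estimate with its confidence interval so that it can be read against 3.0 units. Keep a rank test as a named sensitivity analysis.

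The cost is a change of wording in Statistical analyses. The baseline score is already collected, conduct does not change, and the evaluable target stays at 102. The one downside is that a rank test can have more power under strong skew (84.1% against 79.7% at skewness -1 above). Keeping it as a sensitivity analysis leaves that information visible.

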### Outcome measures

To determine the health-related quality of life (primary outcome), the general questionnaire FACT G version 4 is used. It contains a summary of 27 items divided into four primary focal points relating to quality of life.

To measure secondary outcomes such as ability to work, the days of sick leave will be recorded at work, as well as the help needed with daily chores. The direct correlation between self-management and perceived self-efficacy is measured with the Jerusalem & Schwarzer questionnaire [23]. The satisfaction of patients with the care received is measured using the Patient Assessment of Chronic Illness Care (PACIC 5-A), which has been developed to assess congruency of provided health care to the Chronic Care Model (CCM). Table 2 gives an overview of the measuring tools for the primary and secondary outcomes (table 2). Data is collected at the beginning of the trial, and after 3, 6 and 12 months.

**Table 2 T2:** Overview of measuring tools/measuring time

Outcomes	Measuring tool	Point in time
**Primary Outcome** Quality of life	FACT G	Months 0, 3, 6, 12

**Secondary Outcomes**		Months
Employability	Questionnaire	0, 3, 6, 12
Self - efficacy Unplanned consultations (GP/oncologist, specialist) and hospitalisation Satisfaction with medical care Type, number of rehabilitation measures	Questionnaire self-efficacy expectation by Jerusalem & Schwarzer Number of consultations/rehabilitation- and support measures Questionnaire PACIC 5-A Questionnaire- patient logbook	

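### Adjustment of the primary FACT-G comparison depends on an undefined baseline imbalance, and is not fixed in advance for baseline FACT-G and tumour-type stratum

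*Protocol article*

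**What the plan says.** All of this is in the protocol article.

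- **Comparison.** Statistical analyses: "Primary and secondary outcomes will be compared between groups to investigate the effect of the case management on oncology rehabilitation". The kind of test is chosen after a Shapiro-Wilk check ("using parametric or non-parametric tests as appropriate"). No covariate is named for this comparison.
- **Adjustment.** The same section adds multiple regression to deal with imbalance between the arms, and gives the selection rule: "measures that show any difference in baseline characteristics will be included into the model as potential confounders".
- **Baseline.** Outcome measures: "Data is collected at the beginning of the trial, and after 3, 6 and 12 months". Table 2 lists FACT-G at month 0. Randomisation places this measurement before the allocation is known: "After the inclusion of a patient in the trial and the baseline assessment, the study nurse receives information concerning the allocation".
- **Strata.** Randomisation: "allocation will be stratified according to the type of carcinoma". The groups are breast, colon, Hodgkin and non-Hodgkin lymphoma, and other tumours.
- **Planning figures.** Sample size: "a variation of 3.0 units in the FACT-score is considered clinically relevant"; "The standard deviation of FACT is 5.4 according to literature". Significance level 0.05 and power 0.8 give 102 patients; with 30% drop-out, 132 are to be enrolled.

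**The concern.** A baseline score adds precision because it predicts the 12-month score. That holds whether or not the arms happen to differ at baseline. The stated rule selects covariates on the observed imbalance, which is a different property.

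Three consequences follow.

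1. Tumour type is balanced by the stratified allocation, so it is unlikely to show a difference. The rule would usually leave out the one factor that the design itself singles out.
2. The rule does not define a difference. It could mean a significance test, a chosen threshold or any numerical gap. The covariate list is therefore settled only after the data are seen.
3. The section does not rank the two analyses. If the test and the regression disagree, the text does not say which one answers the primary question.

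At stake are avoidable loss of power on the primary outcome and an analysis that is not fully fixed in advance. The same wording governs self-efficacy and the PACIC-5A score, which are also collected at month 0.

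**Working it through.** **Inputs from the article:** difference 3.0, SD 5.4, alpha 0.05, power 0.8, two arms, 132 enrolled, 30% drop-out. Sidedness is not stated, and 1:1 allocation is inferred from two arms and block sizes of 2 and 4.

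**Inputs assumed:** correlation r between baseline and 12-month FACT-G, 0.3 to 0.7; share of outcome variance explained by tumour type, 2% to 10%. The article gives neither.

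**Step 1: reproduce the plan's figure.** n per arm = 2 × (1.960 + 0.842)² × 5.4² / 3.0² = 50.9, rounded up to 51, so 102 in total. This matches the article. A one-sided test would give 82, so the calculation is two-sided. It is the formula for an unadjusted comparison of two means.

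**Step 2: completers.** 132 × 0.70 = 92.4, or about 46 per arm.

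**Step 3: adjustment for baseline FACT-G in every case.** Residual SD = 5.4 × √(1 − r²). Power at 46 per arm is from the two-sample t distribution. Power at 51 per arm and the total N for 80% power use the normal formula of step 1.

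| r | Variance removed (r²) | Residual SD | N for 80% | Power, 46 per arm | Power, 51 per arm |
|---|---|---|---|---|---|
| 0 (unadjusted) | 0% | 5.40 | 102 | 0.750 | 0.801 |
| 0.3 | 9% | 5.15 | 94 | 0.789 | 0.837 |
| 0.4 | 16% | 4.95 | 86 | 0.820 | 0.865 |
| 0.5 | 25% | 4.68 | 78 | 0.861 | 0.900 |
| 0.7 | 49% | 3.86 | 52 | 0.958 | 0.975 |

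**Step 4: the plan's conditional rule, reading a difference as p < 0.05 at baseline.** Under randomisation, baseline FACT-G then enters in about 5% of trials. Simulation with 46 per arm, normal data and 8,000 trials per scenario:

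| r | Power: t-test | Power: conditional rule | Power: always adjusted | Type I error: conditional rule |
|---|---|---|---|---|
| 0.3 | 0.746 | 0.748 | 0.782 | 0.046 |
| 0.5 | 0.754 | 0.763 | 0.857 | 0.043 |
| 0.7 | 0.758 | 0.775 | 0.959 | 0.037 |

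The conditional rule gains at most about two points over the plain test. It is also somewhat conservative. Always adjusting keeps type I error at 0.049 to 0.051.

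**Step 5: the same rule, reading a difference as any numerical gap.** Two arm means almost never coincide, so baseline FACT-G would nearly always enter and most of the gain in step 3 would be kept. By the same logic, so would almost every demographic and medical item listed under Patient characteristics, whether prognostic or not, in a model with about 92 completers.

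**Step 6: tumour type alone.** If it explains 2%, 5% or 10% of the variance, N for 80% power is 100, 98 or 92. Power at 51 per arm is 0.81, 0.82 or 0.84. An unadjusted test after stratified allocation then has true size of about 0.048, 0.044 or 0.039 against a nominal 0.05, because its standard error is slightly too large for the design.

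**The case against.** A reader might infer that the plan ignores baseline FACT-G and the strata altogether. The text does not support that: the regression sentence lets either enter when it differs between arms. A reader might also take the unadjusted test to be the declared primary analysis. The sample-size formula fits that reading, but the section never says so. Nor does it say whether 12-month scores or changes from baseline are compared.

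The power loss depends on how one undefined word is read. Under the literal reading in step 5, most of it disappears. It also depends on a correlation that the article does not give; at 0.3 the gain is only about four points and stops just short of 80%. The strata contribution is small. The shortfall from 80% at 92 completers comes from the drop-out allowance, which is a separate matter.

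Finally, an article may leave the exact covariate list to a full protocol or analysis plan, so silence alone would be no finding.

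All of this stands, and it limits the size of the point. It does not remove it. The article is not silent: it states a selection rule, and that rule depends on the observed data, is undefined and is unrelated to prognostic value under either reading.

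**Conclusion.** The point holds in a limited form. The fault is that adjustment is triggered by an undefined imbalance, with no statement of which analysis is primary.

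If a difference means a significant baseline test, at 46 per arm the plan forgoes about 4, 11 or 21 percentage points of power at assumed correlations of 0.3, 0.5 or 0.7 (0.75 against 0.79, 0.86 or 0.96 in step 3), and the conditional rule wins back almost none of it. If it means any numerical difference, little power is lost, but the model becomes crowded and is not known beforehand. Nearly all the available gain comes from baseline FACT-G; including the strata mainly corrects a slightly conservative standard error.

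The calculations do not show bias or inflated type I error: where the size departs from 5%, it is below it. The planned comparison is therefore not invalid. This is an inexpensive improvement that should be made. The figures rest on the article's 3.0 and 5.4 taken as given, on 1:1 allocation and a two-sided test, and on the assumed correlations.

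**What to change.** Replace the imbalance-driven selection sentence in Statistical analyses with one pre-specified primary model: a linear regression of 12-month FACT-G on randomised arm, baseline FACT-G and tumour-type stratum, used whatever imbalance is observed. Report the adjusted mean difference with its 95% confidence interval, and state that this is the primary result. Use the same form for self-efficacy and PACIC-5A, each with its own baseline value. Keep the unadjusted test as supportive.

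The cost is a change of wording and about four degrees of freedom (one for baseline, three for four strata). No new data are needed, because baseline and stratum are already recorded before allocation.
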